### Ethical aspects

Informed consent will be obtained from the participants before they are aware of which group they are to be included in. Before they give their consent, the patients will be provided with a general overview of the aims and characteristics of the study and the psychological and pharmacological intervention. They will also be informed that they will be participating voluntarily, and that they can choose to withdraw at any time with the guarantee that they will continue to receive the treatment considered most appropriate by their GP. The study follows Helsinki Convention norms and posterior modifications and the Declaration of Madrid of the World Psychiatric Association. For ethical reasons, patients allocated to Treatment as Usual will be offered the possibility to complete the psychotherapy program. The Study Protocol was approved by the Ethical Review Board of the regional health authority (ref: PI10/039).

### Analysis strategy

#### Analysis of clinical efficacy

The analysis will be per intent to treat and will follow CONSORT recommendations [54]. First, the three groups will be compared in order to verify that there are no significant differences among them at baseline to confirm they are comparable after randomization.

For comparisons, the ANOVA for continuous variables and the Chi-squared test for categorical variables will be used. Non-parametric tests may also be used. To confirm main hypothesis, an analysis of variance (ANOVA) of repeated measures, including all the assessments over the time, will be carried. The main outcome, scoring of BDI-II, will be used as continuous variable. Models will include adjustment by baseline value of BDI-II and any other variable that show differences among groups at baseline. Possible interactions Group × Time will be assessed using Mixed Factorial Anova (3 × 4: 3 groups by 4 temporal moments). Other linear regression models will be used to compare differences in BDI-II scoring among groups for each assessment over the time compared to baseline. Similar analysis will be carried out for secondary outcomes. For missing values a sensitivity analysis will be used to estimate the effect of missing values. Those valued will be replaced using different systems such as last registered values and imputations.

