### Randomization, allocation and masking of study groups

Each patient will be allocated to either one of the three groups using a computer-generated random number sequence. We will use block allocation, with 3 blocks (one for each participating region) including 150 patients per block, with about 50 patients per arm. The allocation will be carried out by an independent person, belonging to REDIAPP (Primary Care Prevention and Health Promotion Research Network), who is not involved in the study. The method used to implement the random allocation sequence will be a central telephone. The sequence will be concealed until interventions are assigned. Patients will agree to participate before the random allocation and without knowing which treatment they will be allocated to. Study personnel conducting psychological assessments will be masked to participants' treatment conditions.

The researcher that administers baseline assessments will be unaware of the treatment group to which the patient belongs to. This researcher will be different from the one that administer the questionnaires over the study. GPs will be also unaware, as long as possible, of the arm to which the patient has been randomized, since their treatment should be exclusively based on the recommendations of the guides for the treatment of depression. The flowchart of the study is summarized in Figure 1 (Insert by here).

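### Beyond baseline BDI-II, covariates are chosen by chance imbalance between randomised arms, a rule that will almost never admit region, the allocation block

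*Protocol article*

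**What the plan says.** The Analysis of clinical efficacy section opens with a baseline check: "the three groups will be compared in order to verify that there are no significant differences among them at baseline". The stated purpose is to confirm that randomisation produced comparable arms. The methods follow: "For comparisons, the ANOVA for continuous variables and the Chi-squared test for categorical variables will be used", with non-parametric tests as an option. The main hypothesis is tested by repeated-measures ANOVA, and the covariate rule is explicit: "Models will include adjustment by baseline value of BDI-II and any other variable that show differences among groups at baseline". Secondary outcomes are to be analysed similarly. The section gives no list of candidate variables and no threshold for a difference.

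The section on randomisation, allocation and masking describes individual, computer-generated, centrally concealed allocation: "Each patient will be allocated to either one of the three groups using a computer-generated random number sequence". It is organised by region: "We will use block allocation, with 3 blocks (one for each participating region) including 150 patients per block", with about 50 patients per arm in each block. Region is not named in the analysis section. The Sample size section describes the same step as cluster randomisation, although it too places one third of each centre's patients in each arm.

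**The concern.** When patients are allocated at random with concealment, any baseline difference between arms is a chance difference. A test of it has no open hypothesis to decide, and a non-significant result does not show balance.

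Using the result to choose covariates has three consequences:

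- A strong predictor of later BDI-II that happens to be balanced is left out, although adjusting for it would improve precision. A variable unrelated to outcome that happens to differ is put in.
- Apart from baseline BDI-II, the content of the primary model is unknown until someone has looked at baseline data by arm. With no candidate list or threshold, and with the choice of test open, the analyst has discretion in a confirmatory model.
- The rule runs against the design. Regional blocks exist to balance region across arms, so a rule that admits only imbalanced variables will hardly ever admit region.

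At stake are a fixed primary model and some precision.

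**Working it through.** The plan gives no figure of its own on this point, so there is none to reproduce. Two quantities can be sized, each on stated assumptions.

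**1. How often chance alone would add a covariate**

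- Candidates: the protocol lists six socio-demographic variables, and Table 1 adds baseline SF-12, EQ-5D and service use. I take k = 6 to 12.
- Assumptions: each is tested at 0.05 (the protocol gives no level), and the tests are independent.
- Formula: P(at least one selected) = 1 − 0.95^k.
- Results: k = 6: 26%; k = 8: 34%; k = 10: 40%; k = 12: 46%.

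This is how often the final model would contain an extra covariate chosen by chance. It is not an error rate for the treatment comparison. Correlated baseline measures would change it.

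**2. What leaving region out costs**

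Let r be the share of BDI-II variance explained by region after baseline BDI-II is in the model. The documents give no value, so r is assumed. With arms balanced within region, the true variance of the treatment difference contains only the fraction 1 − r, while a model without region estimates its standard error from the whole.

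- Reported SE / true SE = 1/√(1 − r).
- r = 0.02: 1/√0.98 = 1.010, so 1.0% too large.
- r = 0.05: 1/√0.95 = 1.026, so 2.6% too large.

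For error rates I use the Sample size section's 100 evaluable patients per arm, effect of 0.40 SD and one-tailed 0.05. In SD units the reported SE is √(2/100) = 0.1414, and the true SE is 0.1414 × √(1 − r).

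- Type I error without region = 1 − Φ(1.645/√(1 − r)).
- Power without region = Φ((0.40 − 1.645 × 0.1414)/true SE).
- Power with region = Φ(0.40/true SE − 1.645).

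| Assumed r | Type I error, region omitted | Power, region omitted | Power, region included |
|---|---|---|---|
| 0 | 0.050 | 0.882 | 0.882 |
| 0.02 | 0.048 | 0.884 | 0.887 |
| 0.05 | 0.046 | 0.888 | 0.896 |
| 0.10 | 0.041 | 0.894 | 0.909 |

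The base power of 0.88 is what these one-tailed inputs give at 100 per arm. Its difference from the stated 0.80 is a separate matter and does not affect this point.

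**3. Both parts together**

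A simulation used three arms and three regions balanced within region, 102 patients per arm, eight weakly prognostic baseline covariates, one-sided 0.05, and covariates entered only if a baseline test gave p < 0.05. At least one covariate entered in about 34% of trials.

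| Region share of variance | Type I error: protocol rule | Type I error: region in model | Power at 0.35 SD: protocol rule | Power at 0.35 SD: region in model |
|---|---|---|---|---|
| 5% | 0.040 | 0.046 | 0.81 | 0.82 |
| 10% | 0.039 | 0.050 | 0.81 | 0.83 |

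With region plus all eight covariates fixed in advance, power was 0.85 and 0.86. That further gain belongs to eight hypothetical predictors and promises nothing for any particular variable in this trial. With no regional effect, type I error under the protocol rule was 0.052 over 6,000 trials, within simulation error of 0.05.

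**The case against.** The strongest reply has four parts.

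- **Baseline BDI-II is already fixed.** The most obvious prognostic covariate is prespecified, so only the additional ones are data-driven. This stands; it would be wrong to read the plan as choosing all its covariates from the data.
- **The adjustment sentence speaks of differences, not significant differences.** This also stands. The test-based reading comes from the sentences just before it. If no test is meant, the criterion is less defined still, so the point survives either way.
- **Silence about region in a condensed article is not exclusion.** Nothing in the text forbids a region term, and a full protocol or analysis plan may include one. A reader might infer that the design is knowingly ignored; the document does not show that. It does state a rule for adding covariates, and that rule would almost never reach region.
- **The harm is small and conservative.** This stands. A reader might infer from data-driven covariates that treatment estimates are biased or false positives more frequent. Selection uses baseline data, not outcomes, and the calculations put type I error at or below nominal, apart from simulation noise. Likewise, 40% is the chance of an extra covariate, not of a wrong conclusion.

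The region argument also depends on how allocation works, and the document describes that in two ways. One third per arm within each centre is compatible with region as a stratum, but the wording needs settling.

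**Conclusion.** The concern holds in limited form. The protocol states a rule that chooses every covariate beyond baseline BDI-II from chance differences between randomised arms. The baseline comparison cannot do the job assigned to it, and the primary model is not fixed until baseline data have been examined by arm. That part needs no numerical assumption.

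The region part is conditional. If region predicts BDI-II beyond baseline and arms are balanced within region, omitting it makes the standard error about 1.0% to 2.6% too large for an assumed 2% to 5% share of residual variance. At 5%, power at 0.40 SD is 0.888 instead of 0.896 and one-sided type I error is 0.046 instead of 0.050. This is a small conservative loss that can be avoided at no cost. It does not threaten the trial's validity.

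**What to change.** In Analysis of clinical efficacy:

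- Describe baseline characteristics by arm with means and standard deviations or counts, and drop the significance tests.
- Replace the clause admitting "any other variable that show differences among groups at baseline" with a fixed adjustment set for all efficacy models: baseline BDI-II and region.
- Name any further prognostic covariates, chosen for expected association with outcome, before unblinding.
- Report adjustment for observed imbalance only as a labelled sensitivity analysis.

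Reconcile the Sample size section's cluster randomisation with the randomisation section's individual allocation within regional blocks.

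The cost is wording only. Region is known from allocation and baseline BDI-II is already collected, so no new data or patients are needed.

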### Sample size

The sample size of this study was based on the expected difference on the primary outcome variable, i.e. depressive symptoms, between the intervention groups and the Treatment as Usual group at post-test. Based on a power of 0.80 in a one-tailed test, an alpha of 0.05, we need 100 subjects in each condition to show an effect-size of 0.40.

Therefore, the total sample size was determined at 300. This sample size also allows calculating clinically significant difference in the main outcome variable, Beck Depression Inventory II. Based on previous studies [36], this difference has been placed at 5 points. It allows changing scoring from normality to mild depression or from mild to moderate depression. Taking account an expected withdrawal rate of 30% according to previous studies [9-14], a sample size of 450 patients (150 by arm) was calculated. The three participating health centers will select 150 patients with cluster randomization to allocate one third in each of the three arms.

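### The sample size is built on two programme-versus-ITAU contrasts at post-test, but the main hypothesis is confirmed by an all-visit ANOVA with no deciding effect or visit fixed

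*Protocol article*

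**What the plan says.** The Sample size section bases the calculation on the expected difference in depressive symptoms "between the intervention groups and the Treatment as Usual group at post-test". The error rates are: "Based on a power of 0.80 in a one-tailed test, an alpha of 0.05". The result is: "we need 100 subjects in each condition to show an effect-size of 0.40". After allowing for 30% withdrawal, "a sample size of 450 patients (150 by arm) was calculated". Nothing is said about dividing alpha between the two programmes.

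The section on analysis of clinical efficacy describes the confirmatory step: "To confirm main hypothesis, an analysis of variance (ANOVA) of repeated measures, including all the assessments over the time, will be carried". It adds a mixed factorial ANOVA of 3 groups by 4 times for the Group × Time interaction, adjustment for baseline BDI-II, and the possible use of non-parametric tests. It continues: "Other linear regression models will be used to compare differences in BDI-II scoring among groups for each assessment over the time compared to baseline". It does not say whether the Group effect, the Group × Time effect or a contrast at a given visit settles the main hypothesis.

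The visit schedule also varies. The Abstract has baseline, 3 and 12 months. The Instruments section has baseline, post-treatment, and 3 and 12 months counted from inclusion. The footnote to Table 1 counts 3 and 12 months from the end of treatment. The Interventions section expects the programme to take most people about 3 months.

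**The concern.** The two sections differ in three ways. The sample size assumes a directional test, whereas an F test across three groups has no direction. It concerns each programme against ITAU, whereas the ANOVA compares three groups at once. It concerns one visit, whereas the ANOVA uses all visits, and the 3 × 4 layout counts baseline as one of them.

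Two things are at stake. The power of 0.80 was calculated for a test that the analysis does not name as confirmatory, and the named test can have much lower power. Also, the same data could confirm or fail to confirm the main hypothesis depending on which effect is read, and that choice remains open until the results are known.

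**Working it through.** **Inputs.** From the Sample size section: standardised effect 0.40, power 0.80, one-tailed alpha 0.05, 100 per arm, 150 per arm after 30% withdrawal. Evaluable per arm: 150 × 0.7 = 105. From the analysis section: 3 groups, 4 times. Assumed, because the document does not give them: between-visit correlation ρ = 0.5 (0.7 as a check), equal variances, both programmes equally effective, no difference at baseline.

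**The plan's own figure.** n per arm = 2(z₁₋α + z₀.₈₀)² / 0.40².
- One-sided 0.05: 2(1.645 + 0.842)² / 0.16 = 77.3, so 78 per arm. Power at 100 per arm is 88.2%.
- One-sided 0.025 (the same as two-sided 0.05): 2(1.960 + 0.842)² / 0.16 = 98.1, so 99 per arm. Power at 100 is 80.7%.

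The stated 100 therefore does not follow from one-tailed 0.05. It matches one-sided 0.025.

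**Error over the two contrasts.** The two contrasts share the ITAU arm, so with equal arms their correlation is 0.5. P(at least one false claim) = 1 − P(Z₁ ≤ z, Z₂ ≤ z).
- Each at one-sided 0.05 (z = 1.645): 8.8%.
- Each at one-sided 0.025 (z = 1.960): 4.5%.

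**Power of the ANOVA Group effect, 105 per arm.** Let δ̄ be the programme effect averaged over the four times. A patient's mean over four visits has variance v = (1 + 3ρ)/4 = 0.625. With group means (δ̄, δ̄, 0), the squared deviations sum to (2/3)δ̄², so the noncentrality is λ = 105 × (2/3) × δ̄² / 0.625, on 2 and 312 degrees of freedom.
- Effect at post-test only (0, 0.4, 0, 0): δ̄ = 0.100, λ = 1.12, power about 14% (simulation gave 13% to 14%).
- Fading effect (0, 0.4, 0.3, 0.2): δ̄ = 0.225, λ = 5.67, power about 55% (simulation 56%).
- Sustained effect (0, 0.4, 0.4, 0.4): δ̄ = 0.300, λ = 10.08, power about 82%.

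At ρ = 0.7 the three figures are 12%, 46% and 72%.

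**Power of Group × Time, same patients.** λ = 105 × (2/3) × Σ(eₜ − δ̄)² / (1 − ρ), where eₜ is the effect at time t.
- Post-test only: Σ = 0.12, λ = 16.8, power about 88%.
- Fading: Σ = 0.0875, λ = 12.25, power about 74%.

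**If baseline is a covariate only.** The plan both adjusts for baseline and counts it among the four times. With baseline as covariate and three later visits, v = (1 + 2ρ)/3 − ρ² = 0.417. The Group effect then has about 32% power for post-test only (δ̄ = 0.133, λ = 2.99) and about 94% for the fading pattern (δ̄ = 0.300, λ = 15.12).

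**Power of one post-test contrast at 105 per arm.** Φ(0.40 × √(105/2) − z): about 89% at one-sided 0.05 and 82% to 83% at one-sided 0.025. If a significant omnibus test at post-test is required first, followed by a two-sided 0.05 contrast, simulation gives 78% to 79% when the third arm equals one of the two, and 72% to 73% when the programme effects are 0.4 and 0.2.

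**The case against.** The best reply is that the article does name a confirmatory analysis, the repeated-measures ANOVA, and calls the regressions merely other models. That is correct. A reader might infer that there is no confirmatory test at all, or that any pair of arms at any visit could be claimed as confirmation. The text supports neither. Only the ANOVA is tied to the main hypothesis, comparison among groups is not a statement that every pair is tested, and the sentence on non-parametric tests may concern the baseline comparison.

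A reader might also infer that the trial's error rate is simply well above 5%. That depends on the decision rule. The 8.8% applies if either contrast at one-tailed 0.05 is enough. If a significant F test had to come first, simulated false programme claims under no effect anywhere were about 4.1% to 4.5%. The article states neither rule.

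It can also be said that gating and alpha sharing belong in an analysis plan that is not shown. As missing detail they would be no finding. But the two sections contradict each other in what they state, and further detail cannot make both describe one test.

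Finally, 100 per arm happens to match a split of one-sided 0.05 over two contrasts. The article does not claim such a split and states 0.05.

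**Conclusion.** The point holds as an inconsistency that should be corrected. The trial is sized for two post-test contrasts, each at one-tailed 0.05, and confirmed by an all-visit ANOVA in which no effect or visit is decisive. On the sample-size section's own test, the chance of at least one false programme claim is 8.8% under no effect.

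The Group effect can fall far below the stated 0.80: about 14% or 55% power for a vanishing or fading effect in the 3 × 4 layout. Group × Time has about 88% and 74% for the same patterns, so the choice between them matters. The low Group figures rest on the assumed correlation, the assumed course of the effect and baseline being a time level. A sustained effect gives about 82%, and using baseline only as a covariate removes most of the loss for the fading pattern (94%) but not for an effect at post-test only (32%). It would go too far to say that the ANOVA is always underpowered. What the documents show is that its power was not what the calculation addressed.

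**What to change.** In the section on analysis of clinical efficacy, name the two programme-versus-ITAU contrasts at post-test, estimated from the longitudinal model, as the confirmatory tests. Define post-test once, and reconcile the visit schedules in the Abstract, the Instruments section and the Table 1 footnote. State whether baseline is a covariate or a time level.

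Control the error over the two contrasts. One simple way is one-sided 0.025 each: overall error about 4.5%, power about 82% at 105 per arm, so the stated 0.80 is kept with 150 per arm. The Sample size section should then state that alpha, which also fits its figure of 100. If low intensity versus self-guided is to be confirmatory too, an omnibus group test at post-test at 5%, followed only if significant by two-sided 5% pairwise contrasts, controls the error across three groups.

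Label the all-visit F tests, later visits, per-visit regressions and non-parametric tests as supportive.

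No patients or visits are added. The cost is power at an effect of 0.40: from about 89% under the stated one-tailed 0.05 to about 82% with the split. With the omnibus gate it falls to about 78%, or about 72% if the programme effects are 0.4 and 0.2, both below the 0.80 target.

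### Baseline BDI-II is both one of four outcome time points and a covariate in the confirmatory model, so a group main effect from that model understates the mean follow-up effect (by 25% with complete data)

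*Protocol article*

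**What the plan says.** In the protocol article, Analysis of clinical efficacy, three statements sit in one paragraph.

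- The test of the main hypothesis: "an analysis of variance (ANOVA) of repeated measures, including all the assessments over the time, will be carried".
- The adjustment: "Models will include adjustment by baseline value of BDI-II", together with any variable found to differ between groups at baseline.
- The layout, given where Group × Time is introduced: "Mixed Factorial Anova (3 × 4: 3 groups by 4 temporal moments".

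The Instruments section lists baseline, post-treatment, 3 months and 12 months. That makes four assessments including baseline and three without it.

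The Sample size section rests on the difference "between the intervention groups and the Treatment as Usual group at post-test". For the clinically significant difference on the BDI-II it says "this difference has been placed at 5 points".

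The efficacy paragraph also plans further linear regressions that compare the groups at each assessment relative to baseline. It does not say whether the main hypothesis is decided by the group main effect, by Group × Time or by a contrast at one visit.

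**The concern.** A score taken before randomisation cannot carry a treatment effect. When it is one of the response levels and the model also conditions on it, the group difference at that level is fixed at zero. Any group effect averaged over the four levels is then pulled towards zero by a visit that says nothing about treatment.

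At stake is the meaning of the estimate. The trial sets 5 BDI-II points as clinically significant and sizes itself on a post-test difference. A group main effect averaged over four visits, one of them pre-treatment, cannot be set against that threshold. A programme that meets the criterion could seem to miss it.

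**Working it through.** **Inputs from the article.** Four time points, including baseline (Instruments; Analysis of clinical efficacy). Baseline BDI-II as covariate (same paragraph). A 5-point relevant difference and 30% withdrawal (Sample size). The article gives no SD, no correlation between visits and no expected effect by visit.

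**The plan's own figure.** The article gives no figure for dilution. Its nearest figure is the sample size: "Based on a power of 0.80 in a one-tailed test, an alpha of 0.05, we need 100 subjects in each condition". The standardised difference assumed there is 0.40. A two-sided t-based calculation gives 99.1 per arm, which agrees with 100; the one-sided one gives 78. That mismatch is a separate matter and does not enter what follows. The relevant fact is that the calculation concerns a single visit, post-test.

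**Step 1: the adjusted main effect.** Let b_post, b_3m and b_12m be the baseline-adjusted group differences at the three follow-ups. Regressing baseline on group and baseline gives a group coefficient of 0. With complete data, the between-patient part of the ANOVA is a regression of each patient's visit mean on group and baseline. Least squares is linear in the response, so:

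- four-visit model: (0 + b_post + b_3m + b_12m)/4
- follow-up-only model: (b_post + b_3m + b_12m)/3
- ratio: 3/4 = 0.75

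For a constant 5-point benefit: (0 + 5 + 5 + 5)/4 = 3.75, against 15/3 = 5. In 1,000 simulated two-arm trials per effect pattern (100 per arm; assumed SD 9 and correlation 0.6), the ratio was 0.7500 in every trial.

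**Step 2: the test.** The four-visit mean equals (baseline + 3 × follow-up mean)/4. Once baseline is in the model, the group coefficient and the residuals are both 0.75 times those of the follow-up model, so the t statistic is the same. In the simulation with a constant 5-point effect it averaged 6.447 in both models.

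**Step 3: the other terms.** Group × Time compares follow-up with baseline: 5 − 0 = 5 for a constant 5-point effect, and the simulated value was 5.01. A regression at one visit estimates b at that visit. Neither is diluted.

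**Step 4: how far 25% depends on conditions.**

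- *Against the post-test effect rather than the follow-up mean:* effects of 5/5/5 give 3.75/5 = 0.75; 5/3/1 give 2.25/5 = 0.45; 2/4/6 give 3.00/2 = 1.50; 5/0/0 give 1.25/5 = 0.25.
- *Dropout:* suppose that the 30% withdrawal all falls before the first follow-up and that the model weights every record equally. Baseline is then 1/(1 + 3 × 0.7) = 1/3.1 = 32% of the records, and the dilution is about 32%.
- *Number of visits:* the Abstract lists only baseline, 3 and 12 months. With three time points the main effect is (0 + b_3m + b_12m)/3, which is two thirds of the follow-up mean, a dilution of 33%.

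**The case against.** The strongest reply is that the diluted quantity is never named as the trial's result. The only effect tied explicitly to the 3 × 4 layout is Group × Time, the usual carrier of a treatment effect when baseline is a response level, and it is undiluted. The per-visit regressions would also give an undiluted post-test difference. The adjustment sentence speaks of models in general and comes before the factorial ANOVA, so the covariate may be meant only for models of follow-up scores. A condensed article may leave the exact terms to a fuller document.

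Much of this stands. A reader might infer that the trial will report a benefit exactly 25% too small. The article does not support that, because it does not fix the reported term and the fraction depends on the conditions in Step 4.

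A reader might also infer a loss of power. With baseline as both response and covariate and complete data, there is none. A loss arises in a different model, the four-visit ANOVA without the covariate, and its size rests on SDs and correlations that the article does not give. Eligibility also restricts baseline BDI-II to 14–28, but no separate consequence has been shown.

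The reply does not remove the contradiction. The article says which analysis confirms the main hypothesis, that it covers all assessments, and that models adjust for baseline. Group × Time is introduced tentatively, and the per-visit regressions are listed as additional models. This is a stated specification that conflicts with itself, not a detail left out.

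**Conclusion.** The point holds. As written, baseline BDI-II enters the confirmatory analysis twice, and a group main effect from it understates the mean follow-up effect.

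The size is 25% for that main effect, relative to the mean of the three follow-up differences, with complete data and equally weighted visits. It is about 32% under the early-dropout assumption above, and 33% if there are only three time points. Relative to the post-test difference, the main effect can be too small or too large, depending on how the benefit changes over time.

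The harm is to the estimate and its comparison with the 5-point threshold. With complete data the p-value of the adjusted main effect is unchanged, and Group × Time and the per-visit estimates are unaffected. Whether the harm reaches the trial's headline result depends on which term is confirmatory, and the article leaves that open.

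**What to change.** In Analysis of clinical efficacy:

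1. Take baseline out of the outcome. Model only the post-baseline BDI-II assessments (three groups by the follow-up visits) with baseline BDI-II as covariate. Alternatively, keep baseline as a response in a constrained longitudinal model with a common baseline mean across arms and no baseline covariate. Choose one.
2. Name the adjusted group difference at post-test, the comparison on which the sample size rests, as the confirmatory contrast.
3. Change the 3 × 4 layout with four time points to match, and reconcile the number of assessments between the Abstract and the Instruments section.

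The cost is about two rewritten sentences in the analysis section plus the reconciled visit list. It needs no new data and no extra patients.
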